# Evaluating the Efficacy and Safety of 48-Week Low-Dose Dienogest Administration in Patients With Dysmenorrhea Caused by Endometriosis: Protocol for a Randomized, Open-Label, Parallel-Group Trial

**DOI:** 10.2196/66246

**Published:** 2025-05-13

**Keywords:** endometriosis, dysmenorrhea, dienogest, clinical trial, open-label

## Abstract

**Background:**

The treatment of endometriosis includes analgesics, hormone therapy, and surgery. Even after surgical removal of endometriotic lesions, the risk of recurrence remains high once the normal menstrual cycle resumes. Therefore, long-term hormone therapy is essential to prevent recurrence. Among hormonal treatments, low-dose estrogen progestin preparations are not recommended for patients older than 40 years due to the increased risk of thrombotic side effects. In contrast, dienogest does not carry a thrombotic risk, making it a suitable option for older patients. Although dienogest requires long-term administration until menopause in patients with endometriosis, data on its long-term efficacy and potential adverse effects remain limited. In particular, comparative studies assessing the safety and effectiveness of long-term use of dienogest at different doses (1 mg/day vs 2 mg/day) have not been conducted, highlighting the need for further investigation.

**Objective:**

The purpose of this study is to investigate the efficacy and the incidence of adverse events of dienogest 1 mg/day after 48 weeks in patients with dysmenorrhea due to endometriosis, compared with dienogest 2 mg/day.

**Methods:**

This randomized, open-label, parallel-group, dose-comparison, multicenter trial follows the SPIRIT (Standard Protocol Items: Recommendations for Interventional Trials) 2013 guidelines and is conducted at 6 centers in Japan. Participants are randomly assigned in a 1:1 ratio to receive either dienogest 1 mg/day or 2 mg/day. The drug is administered for 48 weeks, and its therapeutic effects and side effects are evaluated. Hospital visits include the use of questionnaires, vital sign measurements, imaging studies (magnetic resonance imaging and ultrasound), blood tests, and bone density assessments. The primary endpoint is the change in the pain visual analog scale (VAS) score from baseline to 48 weeks. The VAS is a 10 cm horizontal scale where 0 cm represents no pain and 10 cm represents the maximum imaginable pain; participants indicate their pain level on the scale, and the change is analyzed over time. The target sample size is 88, determined with a noninferiority margin based on existing literature. The protocol was approved by the Nagoya City University Hospital Clinical Research Review Board. Findings will be presented at academic conferences and published in peer-reviewed journals.

**Results:**

Currently, data collection is ongoing. The first participant was enrolled in August 2021. As of March 22, 2025, a total of 88 participants had been enrolled in this clinical trial.

**Conclusions:**

This is the first trial to compare efficacy and safety between 1 mg/day and 2 mg/day of long-term dienogest use in patients with dysmenorrhea caused by endometriosis. Combining diagnostic imaging with patient questionnaires and blood tests allows the determination of efficacy against endometriosis itself.

**Trial Registration:**

Japan Registry of Clinical Trials jRCTs041210016; https://jrct.mhlw.go.jp/en-latest-detail/jRCTs041210016

**International Registered Report Identifier (IRRID):**

DERR1-10.2196/66246

## Introduction

### Background

#### Endometriosis and Dysmenorrhea

Dysmenorrhea is characterized by menstrual pain, nausea, headaches, and related symptoms. One of its primary causes, endometriosis, is an estrogen-dependent disease affecting sexually mature women. This condition significantly reduces quality of life and imposes a substantial socioeconomic burden [1,2].

The incidence of endometriosis has increased due to delayed childbirth and declining birth rates. Hormonal and anatomical changes associated with menstruation and pregnancy significantly influence the risk of endometriosis. Research indicates that nulliparous women with an earlier age at menarche and shorter menstrual cycles are at the greatest risk due to increased lifetime menstrual exposure. Conversely, among parous women, both higher parity and longer lifetime duration of lactation are associated with a decreased risk of endometriosis. Given the current societal trends of delayed marriage and declining birth rates, it is anticipated that the prevalence of endometriosis will continue to rise in the coming years [3,4].

Although the exact etiology and pathogenesis of endometriosis remain unclear, no effective preventive measures exist. Endometriosis can begin at menarche and persist until menopause [5-7], often requiring long-term treatment. Surgical intervention may be necessary, but estrogen exposure in premenopausal patients increases recurrence risk, necessitating prolonged postoperative hormone therapy.

#### Hormonal Treatments for Endometriosis

Hormonal treatments include gonadotropin-releasing hormone agonists, low-dose estrogen progestin therapy, dienogest, and the levonorgestrel-releasing intrauterine system.

Gonadotropin-releasing hormone agonists suppress ovulation, inducing a hypoestrogenic state and alleviating symptoms. However, their use is limited to 6 months due to secondary hypoestrogenic side effects [8]. A low estrogen state, also referred to as hypoestrogenic symptoms, is characterized by significantly reduced circulating estrogen levels. This hormonal reduction can affect various bodily functions, including menstrual regulation, bone metabolism, and cardiovascular health. Common hypoestrogenic symptoms include hot flashes, night sweats, vaginal dryness, mood changes, and decreased bone density.

Levonorgestrel-releasing intrauterine system provides sustained annual efficacy without discontinuation risks but may be more difficult to use in patients with uterine fibroids, adenomyosis, or uterine deformities due to expulsion risks [9].

Low-dose estrogen progestin therapy is associated with an increased risk of thromboembolism, making it less favorable for patients aged 40 years or older [10].

#### Role of Dienogest in Endometriosis Management

Dienogest is a progestin with a lower risk of thromboembolism, making it suitable for patients older than 40 years [11]. It was first approved in Japan in 2007 for the treatment of endometriosis at a dose of 2 mg/day (administered as 1-mg tablets taken twice daily). In 2020, a lower dose of 1 mg/day (administered as 0.5-mg tablets taken twice daily) received approval for the treatment of dysmenorrhea.

However, dienogest 0.5-mg tablets are available only in Japan, and comprehensive knowledge regarding their pharmacological characteristics and potential side effects remains insufficient. In addition, data on the long-term efficacy of dienogest and the side effects associated with low estrogen symptoms are limited [12-14].

#### Consideration of Pharmacological Mechanisms

The therapeutic effects of dienogest on endometriosis are believed to result from multiple mechanisms. Harada et al [15] reported that dienogest reduces estrogen levels, thereby alleviating symptoms of estrogen-dependent endometriosis. In addition to estrogen suppression, dienogest demonstrates high selectivity for progesterone receptors [16] and exhibits antiproliferative activity in isolated human endometrial cells [17]. Furthermore, it has been shown to reduce the proliferative activity of the endometrium in a dose-dependent manner at doses of 0.5 mg or higher [18]. These findings suggest that dienogest’s efficacy may stem not only from lowering serum estradiol levels but also from directly inhibiting endometrial cell proliferation [15].

It has been reported that the use of 0.5 mg tablets results in serum estrogen levels comparable to those of a placebo [19]. However, their efficacy in treating dysmenorrhea has already been demonstrated. If this study shows that 0.5-mg tablets are as effective as 1-mg tablets in treating endometriosis, it may provide new insights suggesting that mechanisms beyond estrogen suppression contribute to the improvement of endometriosis.

The objective of this study is to evaluate the long-term efficacy and safety of low-dose dienogest (0.5 mg/day) compared to the standard 1 mg/day regimen in patients with endometriosis. In particular, we focus on the incidence of adverse effects related to estrogen suppression and the potential for improved treatment adherence with lower doses. Clarifying the dose-dependent relationship between pain relief and adverse effects may help to individualize hormonal therapy strategies for endometriosis.

### Study Objectives

The objective of this study is to compare the efficacy and safety profiles of dienogest 1 mg/day and 2 mg/day in patients with endometriosis-associated dysmenorrhea over a 48-week treatment period. We hypothesize that dienogest can effectively alleviate menstrual pain in these patients without significant adverse effects. Furthermore, by comparing pain improvement, the incidence of adverse effects over the 48-week period, and the occurrence of menopausal symptoms, this study aims to provide insights into optimal treatment selection for individual patients.

## Methods

### Study Design and Participants

This study is a randomized, open-label, parallel-group, dose-comparison, multicenter trial conducted at 6 centers in Japan, in accordance with the SPIRIT (Standard Protocol Items: Recommendations for Interventional Trials) 2013 guidelines (Multimedia Appendix 1). To ensure that participants have endometriosis, only patients diagnosed with ovarian endometriosis were enrolled in the study.

Eligible patients who meet the inclusion and exclusion criteria will be invited to participate in the study by the site investigators (Textbox 1).

Eligibility criteria.
**Inclusion criteria**
Patients who have been diagnosed as having endometriosis (ovarian endometriotic cyst) and have not planned surgery.Patients with dysmenorrhea.Patients who plan to use dienogest for 48 weeks.Patients with a regular menstrual cycle and aged 20 years or older at the time of obtaining consent.Patients who have provided written consent to participate in this study.
**Exclusion criteria**
Patients who have difficulty verbalizing subjective symptoms related to menstruation, etc.Patients currently under treatment for malignant diseases.Patients who have taken dienogest, low-dose estrogen progestin preparations, or other hormonal drugs within 4 weeks of obtaining consent.Patients in whom it has been difficult to diagnose endometriosis.Patients were deemed inappropriate for the study by the study investigator.

### Data Collection and Study Procedures

The study data will be collected through a combination of patient questionnaires (Multimedia Appendices 2 and 3), laboratory tests, bone density measurements, and imaging studies, including preregistration magnetic resonance imaging scans and ultrasound examinations.

Once eligibility is confirmed, study personnel will input patient information into the electronic data capture system to facilitate enrollment and randomization. Randomization using the permuted block method with a block size of 2 or 4 will be stratified based on allocation factors, such as patient age and the presence or absence of uterine adenomyosis.

Treatment will commence on the second to fifth day of the first menstrual cycle following enrollment. Patients will be randomly assigned to receive either dienogest 0.5 mg (1 mg/day group) or dienogest 1 mg (2 mg/day group), administered orally twice daily for up to 48 weeks. Follow-up visits will be scheduled at 4 weeks post enrollment and every 12 weeks thereafter.

At each follow-up visit, comprehensive assessments will be conducted, including patient questionnaires, vital sign measurements, blood tests, and ultrasound examinations to evaluate the size of ovarian endometriotic cysts. A magnetic resonance imaging scan will be performed before study enrollment to establish baseline imaging data. Pain symptoms and estrogen-deficiency symptoms will be assessed through standardized questionnaires. Dysmenorrhea-related pain will be evaluated using the visual analog scale (VAS) and a modified dysmenorrhea score based on Harada et al [20] (Table 1).

The dysmenorrhea score (total score: 0 to 6) is the sum of the subscores on the severity of pain and the use of analgesics.

Estrogen-deficiency symptoms will be assessed using the Kupperman score (Table 2).

**Table 1 table1:** Dysmenorrhea score.

Degree		Definition	Score	
**Pain**				
	None	No pain.	0	
	Slight	Some difficulty with work, household chores, and schoolwork.	1	
	Moderate	Interference with work, housework, or schoolwork to the point of needing to lie down and take a break.	2	
	Severe	Sleeping for more than 1 day and unable to work, do housework, or study.	3	
**Painkiller usage**				
	None	None.	0	
	Slight	Used painkillers for 1 day during menstrual period.	1	
	Moderate	Used painkillers for 2 days during menstrual period.	2	
	Severe	Used painkillers for 3 days during menstrual period.	3	

**Table 2 table2:** Kupperman score.

Symptom	Degree	Evaluation
Hot and sweaty face	3,2,1,0	4
Numbness in the limbs and loss of sensation	3,2,1,0	2
Difficulty falling asleep and waking easily	3,2,1,0	2
Easily agitated and nervous	3,2,1,0	2
Worried and depressed	3,2,1,0	2
Feeling dizzy or nauseous	3,2,1,0	1
Tire easily	3,2,1,0	1
Pain in the shoulders, knees, and knots in the hands and feet	3,2,1,0	1
Headache	3,2,1,0	1
Palpitations	3,2,1,0	1
Feels like ants crawling on the skin	3,2,1,0	1

To determine the score, multiply the “Degree of Symptomatology” (Degree) number by the “Rating Scale” number (Evaluation).

Scoring is classified as follows: mild disease: 16-20, moderate: 21-34, and severe: 35 and above. Degree is defined as strong: 3, moderate: 2, weak: 1, and none: 0.

Patients will be allowed to use analgesics for the management of dysmenorrhea-related pain as needed. Bone density assessments will be conducted twice, at the beginning and end of the study period, using dual-energy x-ray absorptiometry.

### Study Endpoints

The primary efficacy endpoint is the change in VAS from baseline to 48 weeks after administration. The secondary endpoint of effectiveness evaluation is the amount of change in the dysmenorrhea score from baseline to 48 weeks after administration. Another secondary endpoint is the rate of reduction in the size of ovarian endometriotic cysts from the baseline to 48 weeks after administration.

For safety evaluation, an important safety endpoint is the incidence of symptoms related to low estrogen (symptoms other than those listed in the Kupperman score) during the study treatment phase. Symptoms are listed in question number 5 of the questionnaire (Multimedia Appendix 3).

Other safety endpoints include the amount of change in the Kupperman score, the rate of change in bone density, and the amount of change in blood estradiol concentration from baseline to 48 weeks after administration.

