In a study by Momoeda et al [12], bone density changes were measured at 24 and 52 weeks following the administration of 2 mg/day of dienogest. There was a significant reduction in bone mass at both time points (mean –1.6%, SD 2.4%; *P*<.001; mean –1.7%, SD 2.2%; *P*<.001), though the decrease was concluded to be mild. According to Seo et al [13], after one year of administering dienogest 2 mg/day, lumbar spine bone mineral density decreased by 2.2% at 6 months and by 2.7% after 1 year compared to baseline. Furthermore, 75% (45/60) of women experienced significant bone mineral density reduction after one year. Given the high likelihood that dienogest-induced bone density reduction is correlated with estrogen levels [15], it is anticipated that the 1 mg/day group in this study will exhibit less bone loss.

While bone density reduction has been the primary focus of existing studies, other low estrogen symptoms, such as vasomotor symptoms, mood changes, and cardiovascular risks, also warrant evaluation in the context of long-term dienogest administration. Although the frequency of these symptoms is expected to be low with dienogest therapy, this study will assess the incidence and severity between the 1 mg/day and 2 mg/day groups. By analyzing these differences, this study aims to clarify whether dosage variations influence adverse effects beyond bone density reduction and provide insights into dose selection for the treatment of endometriosis-associated dysmenorrhea.

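### Symptoms on the Kupperman list are left out of the whole-period incidence endpoint and are compared between doses only as a week-48 change, so those that come and go earlier enter no named dose comparison

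*Protocol article*

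**What the plan says.** **Collection.** Data Collection and Study Procedures sets the timetable: "Follow-up visits will be scheduled at 4 weeks post enrollment and every 12 weeks thereafter". It adds that "At each follow-up visit, comprehensive assessments will be conducted, including patient questionnaires, vital sign measurements, blood tests, and ultrasound examinations" and that "Pain symptoms and estrogen-deficiency symptoms will be assessed through standardized questionnaires". The instrument is then named: "Estrogen-deficiency symptoms will be assessed using the Kupperman score (Table 2".

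**Endpoints.** Study Endpoints has two layers for low-estrogen effects.
- The important safety endpoint is incidence over the whole treatment phase. It is restricted to symptoms that are not Kupperman items, taken from question 5 of the follow-up questionnaire.
- A second list begins "Other safety endpoints include the amount of change in the Kupperman score, the rate of change in bone density" and closes with "the amount of change in blood estradiol concentration from baseline to 48 weeks after administration". The closing time window governs the list, so the Kupperman endpoint is the change from baseline to week 48.

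**Analysis.** Statistical Analysis compares the incidence endpoint between arms by chi-square. It compares the mean Kupperman score by a difference with 95% CI and names no other visit. Adverse events and side effects are tabulated as frequencies in the safety population.

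**Stated aims.** Study Objectives undertakes to compare the occurrence of menopausal symptoms over the 48 weeks. In the Discussion (Principal Findings), after naming vasomotor and mood symptoms among others, the article says that "this study will assess the incidence and severity between the 1 mg/day and 2 mg/day groups". The note to Table 2 gives severity bands: "Scoring is classified as follows: mild disease: 16-20, moderate: 21-34, and severe: 35 and above". No endpoint uses them.

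**The concern.** The symptoms most typical of estrogen deficiency are Kupperman items: hot and sweaty face, sleep difficulty, agitation and depressed mood. Excluding them from the incidence endpoint avoids double counting, but it leaves them with a single named comparison, a mean change at one late visit. Such a change answers whether the arms differ at the end. It does not say how many patients were affected during treatment, or how badly at their worst, and those are the questions the article sets itself.

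At stake is part of the safety side of the dose comparison. If transient vasomotor or mood symptoms are more frequent at one dose, the named endpoints could show little or no difference although the questionnaires recorded it.

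**Working it through.** **1. The plan's own figure.** Sample Size claims more than 80% power for low-estrogen symptom incidence of 20% versus 50%. With n = 44 per arm, p1 = 0.20, p2 = 0.50 and mean proportion 0.35:

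power = Φ{[(p2 − p1)·√n − 1.96·√(2·0.35·0.65)] / √(p1(1 − p1) + p2(1 − p2))}
= Φ{[0.30·6.633 − 1.96·0.6745] / √(0.16 + 0.25)}
= Φ{(1.990 − 1.322) / 0.640} = Φ(1.043) = 85.2%.

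With 41 per arm it is 82.5%. The claim reproduces. It belongs to the incidence endpoint, though, and so does not cover Kupperman-listed symptoms.

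**2. Which comparison sees which symptom.**

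| Symptom | Whole-period incidence, chi-square | Week-48 mean change, 95% CI | Adverse-event frequency |
|---|---|---|---|
| Not on the Kupperman list | yes | no | if reported as such |
| Kupperman item, present at week 48 | no | yes | if reported as such |
| Kupperman item, resolved by week 48 | no | no | if reported as such |

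The third row is the gap. Statistical Analysis names no test or interval between arms for the adverse-event column.

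**3. Data that could fill it.** Read literally, the visits fall at 4, 4 + 12 = 16, 28 and 40 weeks after enrollment, before the week-48 assessment. Treatment starts at the next menstrual cycle, so the first visit may come soon after the start. That leaves three or four earlier on-treatment questionnaires per completer.

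**4. One patient, by Table 2.** Strong hot flushes score 3 × 4 = 12 and strong sleep difficulty 3 × 2 = 6, total 18, inside the mild band (16 to 20). Suppose she scores 0 at baseline, 18 at an interim visit and 0 at week 48. Her endpoint value is 0 − 0 = 0, and the incidence endpoint does not count her.

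**5. Arm level (illustration only).** Assume Kupperman symptoms occur at the 20% and 50% that the article assumes for low-estrogen symptoms, that each affected patient rises by 18 points, that other patients do not change, and that a share s has resolved by week 48. The documents give neither the rise nor s.
- Week-48 mean difference = 18 × (0.50 − 0.20) × (1 − s) = 5.4 × (1 − s).
- s = 0: 5.4 points. s = 0.5: 2.7 points. s = 1: 0 points.
- The difference in mean worst change stays at 5.4 points, and the difference in patients ever reaching the mild band stays at 30 percentage points, whatever s is, provided a visit falls while the symptom is present.

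**6. Early stopping, for comparison.** Suppose instead that symptoms persist, a share q of symptomatic patients stops, and only those with a week-48 value are analysed. The observed proportion is p(1 − q)/(1 − pq).
- q = 10%: 0.45/0.95 − 0.18/0.98 = 47.4% − 18.4% = 29.0 points; overall loss (5% + 2%)/2 = 3.5%.
- q = 20%: 0.40/0.90 − 0.16/0.96 = 44.4% − 16.7% = 27.8 points; overall loss 7%.

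The planned 5% dropout lies between these, so the true 30-point difference shrinks by only about 1 to 2 points. Unseen transient symptoms, not dropout, carry the argument.

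**The case against.** A reader might infer that early symptoms, and patients who stop because of them, vanish from the safety comparison altogether. The document does not support that. Symptoms outside the Kupperman list are counted over the whole treatment phase and compared by chi-square, and adverse events are counted in the safety population. An early stopper can appear in both, and a troublesome hot flush may be reported as an adverse event. This stands, and it limits the point to Kupperman-listed symptoms.

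Three other extensions also fail.
- Estradiol at every visit is not stated; the text says only that blood tests are done.
- Exclusion of patients without a week-48 value depends on missing-data rules that may lie in the full protocol or analysis plan, neither of which is shown.
- The bone-density losses cited in the Discussion come from other studies at 2 mg/day. They do not show when Kupperman symptoms begin or resolve, and so do not measure this gap.

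It can also be said that the endpoint list is worded as non-exhaustive, that by-visit summaries are not ruled out, and that the Kupperman total is itself a severity score. All true. But the change to week 48 is the only Kupperman comparison the article names, and severity at the final visit is neither incidence nor worst severity. Leaving the bands unused would be a fair choice if another endpoint answered the stated question; none does.

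**Conclusion.** The point holds as a cheap improvement, confined to Kupperman-listed symptoms. As written, the endpoints leave the article's own question about the occurrence and severity of vasomotor and mood symptoms during treatment only partly answered. Symptoms that resolve before week 48 reach no named dose comparison, and only adverse-event counts could record them.

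The size is unknown, because the document does not say how often such symptoms resolve. On the illustrative inputs, the week-48 mean difference falls from 5.4 points to 0 as the resolved share goes from none to all. That is a range under assumptions, not an estimate of bias. The conclusion also rests on the natural reading that the Kupperman items are part of the questionnaire completed at each follow-up visit; the questionnaire itself is not shown. The primary analysis and the sample size are unaffected.

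**What to change.** In Study Endpoints and Statistical Analysis, keep the week-48 Kupperman change and add, in the safety population over all on-treatment questionnaires:
1. each patient's worst change from baseline in Kupperman score, by arm, with the difference in means and 95% CI;
2. the proportion of patients moving to a worse Table 2 band at any visit, by arm, with the difference and 95% CI. Scores below 16 have no band and should be declared the lowest category.

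Both are needed: strong hot flushes alone score 12 and would not reach a band. A by-visit or repeated-measures comparison of the Kupperman score may support these two. Report the number of questionnaires per patient by arm, since a worst value depends on how often a patient was assessed.

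**Cost.** A few more safety tables; no new visits, tests or patients. The real drawback is timing. The trial is open-label, and the Results section says that data collection is finalized (the abstract still calls it ongoing). The additions should therefore be dated and documented before the analysis begins, and labelled descriptive.

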### Statistical Analysis

The primary analysis involves comparing the change in VAS from baseline to 48 weeks between the dienogest 1 mg/day group and 2 mg/day group using the mean difference and its 95% CI. When the lower limit of confidence exceeds –15 (noninferiority margin), the noninferiority of the effect of the 1-mg group to the 2-mg group will be recognized.

For the secondary efficacy endpoint, each of the dienogest 1 mg/day group and the 2 mg/day group will be compared to estimate the difference and its 95% CI for the mean value of dysmenorrhea score and change in endometriotic cyst size from baseline to 48 weeks.

In the safety evaluation, the frequency of low estrogen symptoms during the study treatment period is aggregated, and a 95% CI is calculated that is based on a normal approximation of the binomial distribution. In addition, a chi-square test will be used to compare groups. The 2-sided significance level is 5%.

The frequencies of the occurrence of adverse events and side effects are calculated for the safety analysis target population. As a secondary safety analysis, each of the dienogest 1 mg/day group and 2 mg/day group will be compared to estimate the difference and its 95% CI for the mean value of bone density, Kupperman score, and estrogen concentration. Statistical analyses are performed by R (version 4.1.0; R Foundation for Statistical Computing).

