## Discussion

### Principal Findings

This study aims to demonstrate that dienogest 0.5 mg tablets are as effective and safe as dienogest 1-mg tablets in the treatment of endometriosis. Furthermore, based on the evaluation results from this study, recommendations for the optimal use of dienogest 0.5-mg and 1-mg tablets could be proposed.

Currently, 0.5 mg dienogest tablets are approved for dysmenorrhea, but their effectiveness in improving endometriosis symptoms and lesions remains unclear.

Osuga et al [19] conducted a study comparing dienogest 1 mg/day and 2 mg/day in patients with primary dysmenorrhea and reported equivalent improvements in VAS scores between the 2 groups. However, this study did not include patients with endometriosis-related dysmenorrhea, making it insufficient to evaluate the efficacy of dienogest for endometriosis.

Another study by Osuga et al [22] compared dienogest 1 mg/day with placebo and demonstrated its efficacy in treating dysmenorrhea. However, only approximately 23% of the study population had endometriosis, which is insufficient to fully assess its effectiveness for this condition. Currently, there are no other studies comparing dienogest 0.5-mg tablets with 1-mg tablets for endometriosis, and thus, the findings of this study are expected to provide novel insights into the efficacy and safety of dienogest 0.5-mg tablets for endometriosis.

With respect to serum estrogen levels during dienogest administration, it was observed that estrogen levels did not decrease significantly with a 1 mg/day dosage compared with the placebo group. However, a dose-dependent reduction in estrogen levels was observed [19,24].

Prolonged hypoestrogenic states induced by dienogest therapy may increase the risk of adverse effects such as bone mineral density loss. Estrogen plays a crucial role in maintaining bone homeostasis by promoting osteoblast activity and inhibiting bone resorption by osteoclasts [25].

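### Estradiol is compared as an unadjusted change from baseline in cycling women, which may lose precision; week-48 log estradiol adjusted for baseline would avoid this at almost no cost

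*Protocol article*

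**What the plan says.** Study Endpoints (protocol article) places estradiol last among the other safety endpoints and defines it as "the amount of change in blood estradiol concentration from baseline to 48 weeks after administration". Statistical Analysis says the arms will be compared by a difference with 95% CI for "the mean value of bone density, Kupperman score, and estrogen concentration". It names no baseline covariate, transformation or repeated-measures model for estradiol.

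Three statements describe the baseline:
- The inclusion criteria require "Patients with a regular menstrual cycle and aged 20 years or older at the time of obtaining consent".
- The exclusion criteria rule out recent use of dienogest, estrogen-progestin preparations "or other hormonal drugs within 4 weeks of obtaining consent".
- The only cycle-day rule concerns dosing: "Treatment will commence on the second to fifth day of the first menstrual cycle following enrollment". No cycle day is stated for the baseline blood sample.

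Follow-up visits include "patient questionnaires, vital sign measurements, blood tests, and ultrasound examinations". The article does not say whether each set of blood tests includes estradiol.

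On interpretation, the Discussion reports from cited work that "estrogen levels did not decrease significantly with a 1 mg/day dosage compared with the placebo group", and also that the fall in estrogen depended on dose. The Introduction says of a finding of equal efficacy that "it may provide new insights suggesting that mechanisms beyond estrogen suppression contribute to the improvement of endometriosis".

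**The concern.** In regularly cycling women who are off hormones, a single baseline estradiol value reflects cycle phase as well as the woman's usual level. Subtracting it from the week-48 value carries that variation into the outcome. Subtraction helps only if baseline predicts the week-48 value well enough. After 48 weeks on a progestin, there is no reason given in the article to expect that it does.

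At stake is the precision of the between-arm estradiol contrast. The Discussion links bone loss to estrogen level, and the Introduction raises mechanisms other than estrogen suppression. If the estradiol comparison is needlessly imprecise, a non-significant difference could be taken to mean that both doses suppress equally, when the data were simply too noisy to tell.

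**Working it through.** **The plan's own figures.** The article gives no SD, expected difference or power for estradiol. Its only related figure is the VAS sample size, which reproduces: 2 × (1.96 + 0.84)² × 24.13² / 15² = 40.6, so 41 per group; 41 / 0.95 = 43.2, so 44. This says nothing about estradiol, but it supplies the 41 evaluable patients per group used below.

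**Inputs not in the article (assumptions).** Let k = baseline SD / week-48 SD, and ρ = the correlation between baseline and week-48 values. I take k from 0.5 to 3, ρ of 0 or 0.5, and for illustration a true dose difference of 0.8 week-48 SDs.

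**Step 1: variance.**
- Var(change) / Var(week-48 value) = 1 + k² − 2ρk.
- This exceeds 1 whenever ρ < k/2. For k above 2 it always does, since ρ cannot exceed 1.
- Adjusting for baseline as a covariate gives a factor of 1 − ρ², which never exceeds 1 (apart from one lost degree of freedom).

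**Step 2: power.** At two-sided 5% with n = 41 per group, power ≈ Φ(0.8 / (r × √(2/41)) − 1.96), where r is the square root of the variance ratio.
- Week-48 value alone (r = 1): 0.8 / 0.221 = 3.62, and Φ(1.66) = 95%.
- Change score, k = 1, ρ = 0: r = 1.41, and Φ(0.60) = 73%.
- Change score, k = 3, ρ = 0: r = 3.16, and Φ(−0.81) = 21%.

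The smallest difference detectable with 80% power is 2.80 × √(2/41) × r = 0.62 × r week-48 SDs.

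| k | ρ | Variance ratio | Detectable difference (week-48 SDs) | Power, change score |
|---|---|---|---|---|
| 0.5 | 0 | 1.25 | 0.69 | 90% |
| 0.5 | 0.5 | 0.75 | 0.54 | 99% |
| 1 | 0 | 2 | 0.88 | 73% |
| 1 | 0.5 | 1 | 0.62 | 95% |
| 2 | 0 | 5 | 1.38 | 37% |
| 2 | 0.5 | 3 | 1.07 | 55% |
| 3 | 0 | 10 | 1.96 | 21% |
| 3 | 0.5 | 7 | 1.64 | 28% |

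For comparison, the week-48 value alone has 95% power in every row. The baseline-adjusted analysis has 95% at ρ = 0 and 99% at ρ = 0.5.

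**Step 3: bias.** In 20,000 simulated trials of 41 per group, with a skewed baseline, ρ = 0 and a true difference of −0.8, the change-score estimate was off by only 0.004 on average. Its standard error was 0.53, against 0.22 for the week-48 value. The cost is noise, not bias.

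**Step 4: if the baseline was timed.** Suppose the baseline was drawn on days 2 to 5, with assumed SDs of 17 at baseline and 21 on treatment (pg/mL) and ρ = 0. The SD of change is √(17² + 21²) = 27. The half-width 1.96 × SD × √(2/41) goes from about 9 to about 12. That loss is modest.

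**The case against.** A reader might infer more than the article supports, in four ways.

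- *That the trial leaves the baseline sample untied to cycle day.* The article is silent, and a condensed article commonly leaves sampling day to the full protocol or a laboratory manual. Silence does not show that the sample was untimed. If it was taken on days 2 to 5, the loss may be small, as Step 4 shows.
- *That cycle phase dominates the endpoint, or that the endpoint cannot show dose-related suppression.* Both need estradiol levels by cycle phase, which the article does not give. The result depends on k and ρ: power ranges from 21% to 99% in the table, and with ρ at or above k/2 the change score is no worse than the week-48 value.
- *That a baseline near the cycle low would hide suppression.* That affects the change within an arm. A baseline level shared by both randomized arms cancels in the between-arm difference, which is what is planned.
- *That repeated estradiol values certainly exist.* Blood tests are scheduled at each follow-up visit, but estradiol is not named among them.

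It is also fair to say that the endpoint is listed last and carries no power claim, that bone loss is measured directly, and that the remark on mechanism draws on a cited study's placebo-like estrogen at the lower dose. The Statistical Analysis wording refers to mean estrogen concentration, so a comparison of levels is not clearly excluded.

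What stands is narrower. Study Endpoints does fix a change score, no baseline adjustment is named, and the baseline comes from unsuppressed cycling women. A baseline-adjusted analysis is at least as precise at any correlation and needs no new data.

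**Conclusion.** The point holds as one of precision on a minor safety endpoint. The unadjusted change score is less efficient than the week-48 value whenever ρ is below k/2. Under assumed k of 1 to 3 and ρ = 0, variance rises 2- to 10-fold, and power for a 0.8 SD difference falls from 95% to between 73% and 21%. With lower k or higher ρ the loss shrinks or disappears, and the article does not allow the true size to be worked out.

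Two limits apply. Removing the baseline noise does not remove phase variation at week 48, which may persist in the 1 mg/day arm given the placebo-like estrogen the article reports at that dose. Such variation would also enlarge the week-48 SD, so k would be lower and the relative loss smaller. The randomized comparison remains unbiased, and the primary VAS conclusion is unaffected.

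**What to change.** Define the estradiol comparison as week-48 log estradiol, adjusted for log baseline estradiol, reported as a geometric mean ratio between arms with 95% CI. If estradiol was also measured at the other follow-up visits, use all on-treatment values in a repeated-measures model; this also averages out some of the phase variation during treatment. Report change from baseline descriptively only. State the cycle day of the baseline sample if it was specified or recorded, and align Study Endpoints with Statistical Analysis on whether change or level is compared.

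Add one sentence on interpretation: a non-significant estradiol difference will not be read as equal suppression when the mechanism is discussed, and the confidence interval will be given alongside.

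The cost is a wording change and a slightly larger model, with no new samples. The change score stops being the headline figure. The Results section says the data are already being prepared for analysis, so the change should be dated before estradiol is compared by arm, or labelled post hoc if it is not.
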